#### 4.n. Biostatistical Considerations

The main aim of this study is to evaluate the potential efficacy of 600 mg mifepristone vs. placebo using a signal detection approach commonly used in Phase IIa drug-development trials. The approach was first specified by Simon et al. (1985) and falls within the class of ranking and selection procedures (Gibbons, Olkin and Sobel (1977)). Specifically, a response rate difference that is considered clinically relevant is selected (15% in this study). The sample size is based on providing a pre-specified degree of certainty (90% in this study) that if the response rate difference is observed, the treatment group with the higher response rate has been correctly identified. The analysis of the primary outcome then becomes a binary decision rule (i.e. has the pre-specified response rate difference been observed (yes or no)). The mifepristone 600 mg/day will be compared to placebo over a short duration, as is commonly done in Phase IIa trials. The advantage of using such design for this study is to detect the signal for comparing the 600 mg group vs. placebo while keeping the sample size small. The results generated from this study will provide the basis for a larger, more definitive, Phase III trial when type I error and power are well controlled.

##### 4.n.1. *Expected treatment effect*

The objective of the current study is to assess whether mifepristone 600 mg is potentially effective for PTSD population. Currently, no published studies have examined mifepristone for the treatment of PTSD; however, other major drug studies in PTSD have defined responder status as a 30% reduction in CAPS score. Brady et al. performed a large multisite 12 week, double-blind, placebo-controlled trial to test the efficacy of sertraline; using conservative last observation carried forward, response rates were 53% for the drug group and 32% for placebo group (2000). Similarly, using the intent-to-treat principle, Davidson et al. reported response rates of 60% for the drug group and 38% for the placebo group (2001). The response rates of a double-blind, placebo-controlled pilot study of sertraline in military veterans with PTSD carried out by Zohar et al. were 41% for the drug group and 20% for the placebo group (2002). Marshall et al. evaluated the efficacy and safety of paroxetine for the treatment of patients with chronic PTSD; responder rates were 67% for the drug group and 37% for the placebo group (2001). A similar study carried out by Tucker et al. for paroxetine showed response rates of 58.8% and 38% for the drug and placebo group, respectively (2001). A large study of fluoxetine had response rates of 59.9% for the drug group and 43.8% for the placebo group (Martenyi et. al, 2002).

This study will use a 30% reduction in CAPS total score from baseline to four week follow-up to classify the participants as responders vs. non-responders. The proportion of responders to 600 mg mifepristone will be compared to the proportion of responders to placebo. The referenced studies report response rate differences ranging from 16% to 30% and placebo response rates ranging from 20% to 44%. In the present study, we will consider a 15% difference in the proportion of treatment vs. control group responders to be clinically relevant, as this is the minimum response rate difference in the referenced studies. Since the design of this study is more rigorous, a conservative estimate of the clinically relevant treatment effect is appropriate.

##### 4.n.2. *Sample size determination*

As mentioned above, the sample size has been calculated to provide at least 90% probability that mifepristone 600 mg has been correctly identified as being superior to placebo if the population difference in response rate is at least 15%. Using the calculations provided by Simon et al. (1985) and accounting for a 20% attrition rate which has been reported in other drug studies using a similar population (Bartzokis et al., 2005), a total sample size of 90 is required, or 45 per treatment group. Since the sample size varies according to the responder rate (as well as the magnitude of the difference of interest), and the responder rate for placebo is unknown, we assume a placebo responder rate of 40%, which is at the high end of the studies referenced above. By contrast, in order to have a one-sided Type I error rate of 5% and 80% power to detect the 15% difference between two

groups using a traditional hypothesis testing framework, the study would require 274~344 participants when the placebo responder rate changes from 20% to 44%, after adjustment for a 20% withdrawal rate. If the true population difference in response rate is smaller than 15% (between 10~12%) and if we still consider it clinical significant, the proposed sample size (n=72 completers or 90 with 20% withdrawal rate) will still provide at least 80~85% probability of correctly identifying the superior group.

#### 4.0. Recruitment and Feasibility

Active recruitment will take place over 31 months. To assess the feasibility of recruiting the proposed number of participants the VHA Support Services Center data files for Special Focus Groups were reviewed to determine how many combat veterans with PTSD currently seek care at each of the potential sites. Questionnaires were sent to the sites listed in Table 3 and investigators were asked about their level of interest,

**Table 3: Site Selection**

| VAMC           | Number of PTSD Patients | Number of Previous PTSD Trials |
|----------------|-------------------------|--------------------------------|
| Albuquerque    | 6,594                   | 6                              |
| Birmingham     | 5,289                   | 4                              |
| Bronx          | 1,595                   | 5                              |
| Durham         | 5,775                   | 9                              |
| Pittsburgh     | 1,743                   | 1                              |
| Providence     | 2,647                   | 0                              |
| Salt Lake City | 3,725                   | 2                              |
| San Diego      | 4,733                   | 3                              |
| Temple         | 6,216                   | 0                              |
| Salisbury      | 5,409                   | 7                              |
| Little Rock    | 4,051                   | 1                              |

perceived ability to recruit the requisite number of patients, proposed strategies for recruiting unmedicated and stably medicated participants, their previous experience with PTSD trials, and about any potentially competing studies. Based on their responses and ability to use the local IRB, the four 1.0 FTE sites initially chosen were Albuquerque (terminated in February 2015), Bronx, Durham, and San Diego; the two .50 FTE sites chosen are Salisbury and Little Rock (added in April, 2015).

Researchers at the Bronx site (PIs [name] and [name]) have extensive experience designing and conducting research projects; a study of prolonged exposure therapy at the Bronx site entitled

“Neuroendocrine Correlates of PTSD Before and After Treatment” has enrolled 103 participants since May 2006. “Cortisol Augmentation of a Psychological Treatment in Warfighters with PTSD” recruited 32 participants in the past year. Additionally, the Bronx site has a specialized outpatient PTSD clinic, close links with primary care and the ability to extend recruitment to other local VAs (Manhattan, Brooklyn, Northport, Montrose, East Orange) and community-based outpatient clinics.

The team at Durham has a vast amount of experience with randomized controlled medication studies in PTSD and is well versed in performing the assessments and evaluations that will be used in the present study. For CSP 504, Durham was the second site in terms of recruitment (26 participants in 36 months). Additionally, Durham has participated in eight other trials: 1) CSP 563 recruited 13 participants in 15 months; 2) “A Pilot Randomized Controlled Trial in Sub-threshold PTSD with Paroxetine in Veterans who Served after September 11, 2001” recruited 12 participants in one year; 3) “Bupropion SR for Social and Occupational Dysfunction, Symptom Reduction, and Smoking Cessation in PTSD” recruited 30 participants in two years; 4) “A Placebo-Controlled Evaluation of the Effects of Bupropion for Smoking Cessation in Patients with PTSD” recruited 15 participants in one year; 5) “Lamotrigine in the Treatment of PTSD” recruited 8 participants in one year; 6) “Preliminary Study of Nefazodone in PTSD” recruited 10 participants in one year; 7) “Double-Blind Comparison of Sertraline and Placebo in Outpatients with PTSD” recruited 22 participants in two years; and 8) “Fluoxetine Treatment of PTSD” recruited 11 patients in 18 months.

San Diego is an active research site with a large patient population and high retention and completion rates for participants enrolled in clinical trials. The San Diego site PI, [name], has been an investigator in seminal pharmacotherapy trials in PTSD including: 1) “A Double-Blind, Randomized, Placebo-Controlled, Multi-Center Study of Brofaromine in the Treatment of PTSD;” 2) “Sertraline Treatment of PTSD: A Randomized Controlled Trial;” and 3) “Randomized, Double-Blind Comparison of Sertraline and Placebo for PTSD in a Department of Veterans Affairs Setting.” Additionally, San Diego has participated in three large, multi-site trials: 1) CSP 519 (“Integrating Practice Guidelines for Smoking Cessation Into Mental Health Care for PTSD”) recruited 88 participants in 36 months; 2) CSP 504 recruited 19 participants in 25 months; and 3)

“A Randomized, Placebo-Controlled Trial of Nepicastat for the Treatment of PTSD in OIF/OEF Veterans” recruited 9 participants in 11 months.

Albuquerque has been one of the top recruitment sites for two CSP studies in PTSD: CSP 563 (“Prazosin and Combat Trauma”, having recruited 12 participants in 11 months) and CSP 504 (“Risperidone Treatment for Military Service Related Chronic PTSD”, 14 participants in 30 months). Recruitment was also high in other PTSD studies. However due to low recruitment in this study, this site was terminated in March, 2015. Salisbury and Little Rock were added in April 2015, instead, to help recruitment.

Salisbury VAMC was a very successful site for CSP 563 (“Prazosin and Combat Trauma”). It is also home to a MIRECC dedicated to the study of post-deployment mental health problems including PTSD and mTBI. It has a full research infrastructure and ready-access to the study group of interest.

Little Rock VA has just successfully recruited for and completed several studies of PTSD focused on a similar participant pool. One was a randomized controlled trial of modafanil in OEF/OIF combat veterans with PTSD (25 subjects completed the RCT over an 18 month recruiting period). [name], the site investigator, was also the collaborating psychiatrist on “Telemedicine-based collaborative care for posttraumatic stress disorder: a randomized clinical trial” and facilitated a study examining psychophysiological measures in OIF/OEF veterans.

We propose to enroll 90 participants across multiple VA sites to yield 72 completers based on an estimated attrition rate of 20%. We expect the 3 active sites (Bronx, San Diego, and Durham) to enroll 25~26 patients each over the course of 31 months (0.8 per site per month); and the 2 added sites (Salisbury and Little Rock) to enroll 5~6 patients each over the course of 9~10 months (0.5~0.6 per site per month). The Albuquerque site that was terminated in February 2015 enrolled a total of 2 participants.

Given the data provided by the VHA Support Services Center and the individual study sites, this recruitment goal, which takes into account the challenges of recruiting unmedicated veterans and stably medicated veterans, is feasible.

#### 4.p. Statistical Analyses

##### 4.p.1. Analysis Plan

The randomization will be assessed by comparing the distribution of all baseline characteristics including age, race, marital status, education, duration of symptoms, duration of illness since trauma, overall extent of the psychiatric co-morbidity, whether or not on concurrent psychotropic medications and number of those medications used prior to randomization, baseline total CAPS score, military cohort, and site across the two randomized groups.

##### Primary Outcome:

Primary Analysis of Primary Outcome -The primary analysis for this study will not be based on a hypothesis test; rather, responder rates at one month will be calculated for each of two groups. If mifepristone 600 mg is observed to have at least a 15% higher responder rate than placebo, then we are at least 90% certain we have detected a clinically relevant signal. This analysis will be performed based on a modified intent-to-treat (mITT) principle. All randomized participants will be included in the analyses except for those for whom there is positive proof that they did not take a single dose of study medication (e.g. medication never picked up, full bottle returned, patient immediately declines participation after study medication has been dispensed) or there is positive proof that they are deemed ineligible after randomization and are terminated in the 7-day treatment phase due to safety concern. For patients who do not have one-month CAPS total score, their responses will be estimated using multiple imputation technique as outlined in Molenberghs and Kenward, 2007, Chapter 9 and implemented in the SAS procedure MI using participants aforementioned baseline characteristics and available information at other time points (baseline, 1 week, 12 week). The imputation will be done within each treatment group.

Secondary Analysis of Primary Outcome -The primary outcome will also be compared using chi-square tests. Additionally, logistic regression models will be used to adjust for aforementioned baseline characteristics. The model selection will use a backward elimination procedure and be verified by a forward selection procedure.

Exploratory Analysis of Primary Outcome -The primary outcome will also be explored for subgroups as defined by concurrent psychotropic medication use status and classification prior to randomization. The mITT principle will also be applied in the secondary and exploratory analyses of the primary outcome.

Sensitivity Analysis of Missing Data- In the analyses mentioned above, missing data will be replaced using three additional procedures. The first procedure will entail the assumption of “worst case scenario” where the participants with missing data at week 4 will be deemed non-responders. This approach will provide a conservative test of treatment effects. In the second procedure, the last available information about the primary outcome, if available at week 1, will be used to impute the missing data at week 4 and if missing at both week 1 and 4, participants will be deemed non-responders. The third procedure involves the comparison on all participants whose CAPS score are obtained on week 4.

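### The 90% attached to the primary decision rule belongs to a different rule; the rule as written is met only about half the time when the true difference is 15 points

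*Protocol*

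**What the plan says.** Section 4.n sets a clinically relevant difference ("a response rate difference that is considered clinically relevant is selected (15% in this study") and a 90% degree of certainty "that if the response rate difference is observed, the treatment group with the higher response rate has been correctly identified". It then reduces the primary analysis to one yes/no question: "has the pre-specified response rate difference been observed (yes or no".

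Section 4.n.2 ties the 90% to something else. There "the sample size has been calculated to provide at least 90% probability that mifepristone 600 mg has been correctly identified as being superior" to placebo on the condition that the difference in the population, not in the sample, is at least 15%. The inputs are a placebo rate of 40%, 20% attrition, 90 randomised and 72 completers. The section adds that the probability is still 80–85% if the true difference is only 10–12%.

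Section 4.p.1 gives the rule for the primary analysis: "If mifepristone 600 mg is observed to have at least a 15% higher responder rate than placebo, then we are at least 90% certain" of a clinically relevant signal. Section 4.p, under Secondary Outcomes, carries the same analysis over to the three-month responder rate.

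**The concern.** Two rules are being treated as one.

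- **Selection rule:** choose the arm with the higher observed rate, however small the gap. This is the rule behind the sample size, and its 90% is conditional on the *true* difference.
- **Threshold rule:** declare a signal only if the *observed* difference is at least 15 points. This is the rule in sections 4.n and 4.p.1.

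Sections 4.n and 4.p.1 move the 90% from the first rule to the second and from the true difference to the observed one. For the threshold rule, the 90% is neither the chance of meeting it at the target effect nor the certainty that a relevant effect exists once it has been met.

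The primary objective, and the decision whether to go on to Phase III, rest on this result. A reader of section 4.n.2 would expect a drug with the target effect to be picked out at least nine times in ten; under section 4.p.1 it meets the rule about one time in two. A positive result would also be reported with a certainty that the data do not carry.

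**Working it through.** **Inputs.** From section 4.n.2: placebo 40%, mifepristone 40 + 15 = 55%, 45 randomised per arm, 20% attrition, hence 36 completers per arm. From section 4.n.1: placebo rates of 20% to 44% in the cited studies. Section 4.p.1 imputes missing week-4 outcomes, so the effective number lies between 36 and 45 per arm; both ends are shown.

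**Step 1: reproduce the plan's own figures with the selection rule.**

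n per arm = z(0.90)² × [p₁(1−p₁) + p₂(1−p₂)] / 0.15² = 1.2816² × (0.2400 + 0.2475) / 0.0225 = 35.6, so 36 per arm, 72 completers, and 72 / 0.80 = 90 randomised. This matches.

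Probability of correct selection at 36 per arm, placebo 40%:

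| True difference | Exact, ties split | Normal approximation | Protocol |
|---|---|---|---|
| 15 points | 0.899 | 0.901 | at least 90% |
| 12 points | 0.847 | 0.848 | 85% |
| 10 points | 0.803 | 0.804 | 80% |

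All three stated probabilities come from the selection rule.

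**Step 2: operating characteristics of the threshold rule.** Exact enumeration of two independent binomials, placebo 40%. The smallest qualifying gap is 6/36 = 16.7 points (5/36 = 13.9 falls short), or 7/45 = 15.6 points.

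| True difference | P(observed ≥ 15 points), 36 per arm | 45 per arm |
|---|---|---|
| 0 | 9.3% | 8.1% |
| 10 points | 32.7% | 33.6% |
| 12 points | 39.1% | 40.9% |
| 15 points | 49.3% | 52.3% |
| 20 points | 66.1% | 70.6% |
| 25 points | 80.4% | 85.0% |
| 30 points | 90.5% | 93.9% |

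A 90% chance of meeting the rule needs a true difference of about 30 points with 36 per arm, or 27.5 points with 45. At a true 15 points, moving the placebo rate from 20% to 44% changes the result only within 49.1–49.3% (36 per arm) and 52.3–52.5% (45 per arm).

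**Step 3: is the certainty right once the rule is met?** At 36 per arm the standard error is √(0.4875 / 36) = 0.116. An estimate of 15 points therefore has a 95% confidence interval of 0.15 ± 1.96 × 0.116, about −8 to +38 points. For the smallest passing results, under independent flat priors (an assumption; the protocol states no prior):

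| Result | P(true difference > 0) | P(true difference ≥ 15 points) |
|---|---|---|
| 20/36 vs 14/36 | 0.92 | 0.53 |
| 25/45 vs 18/45 | 0.93 | 0.50 |

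A bare pass supports about 90% certainty that mifepristone is better at all, but not that the effect reaches the size the protocol calls clinically relevant.

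**The case against.** The strongest reply has four parts.

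1. *Section 4.n.2 states the property correctly and the trial is not mis-sized.* This stands. The fault lies in sections 4.n and 4.p.1, but those are the sections that give the rule to be applied.

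2. *Section 4.n claims only that the better arm has been identified, and on a Bayesian reading an observed 15 points does give about 90% for that.* The numbers bear this out (0.92–0.93 at the smallest passing results). It is still not the calculation the protocol makes, and it does not help section 4.p.1, which claims a clinically relevant signal.

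3. *The 50–53% applies only to a bare pass.* This is correct. Averaged over all passing results under uniform priors, the probability of a true difference of at least 15 points is about 0.91. That average depends on a prior the protocol never states and gives much weight to very large effects; a prior concentrated on small effects would give less. Section 4.p.1 attaches its certainty to every passing result, including the smallest, and there it fails.

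4. *Any threshold set at the target effect is met about half the time at that effect, the protocol claims no power for it, and a miss need not end development in an exploratory trial.* All true. A strict threshold with an 8–9% false-signal rate is defensible, and failing the rule is not the same as rejecting the drug. But the general caution about interpretation in section 4.p.1 concerns the significance tests and leaves the 90% statement uncorrected.

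**Conclusion.** The concern holds. The 90% is a property of choosing the arm with the higher observed rate when the true difference is 15 points (0.899 exact with ties split; 0.901 by the normal formula). The rule in sections 4.n and 4.p.1 is met with probability 49–52% at that difference, and 8–9% at no difference with a 40% placebo rate. A result that just meets it gives roughly even odds, under flat priors, that the effect is as large as 15 points. The claim of at least 90% certainty of a clinically relevant signal is therefore wrong as written.

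The operating characteristics assume independent binomial outcomes with 36 to 45 analysed per arm. The 49–52% hardly depends on the placebo rate; the false-signal rate does, falling to 4–5% if the placebo rate is 20%. Neither the sample size nor the choice of a 15-point threshold is at fault, only the guarantee attached to the threshold.

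**What to change.** Before unblinding:

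- In section 4.p.1, delete the statement of 90% certainty.
- In section 4.n, make the 90% conditional on a true difference of at least 15%, in line with section 4.n.2.
- Then settle on one rule and state its own performance:
  - **(a) Keep the observed-15% threshold.** State that, with a 40% placebo rate, a signal is declared with probability about 50% at a true 15-point difference, 80–85% at 25 points and 8–9% at no difference. This is the smaller change and keeps false signals low.
  - **(b) Use the selection rule that the sample size supports.** State how ties are handled. At 36 per arm and 40% versus 55%, splitting ties gives 0.899 and requiring a strictly higher rate gives 0.879. With no true difference this rule selects mifepristone 50% of the time with ties split, or about 45% if strictly higher.
- Under either option, report the difference in responder rates with its confidence interval, and use the same wording for the three-month responder analysis.

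The cost is a change of protocol and analysis-plan text. No extra patients or data are needed. The price is a less favourable stated performance: about 50% in place of 90% under (a), or a much higher false-selection rate under (b).
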